## Abstract

**Background:**

Estimating the risk of malignancy is essential in the management of adnexal masses. An accurate differential diagnosis between benign and malignant masses will reduce morbidity and costs due to unnecessary operations, and will improve referral to a gynecologic oncologist for specialized cancer care, which improves outcome and overall survival. The Risk of Malignancy Index is currently the most commonly used method in clinical practice, but has a relatively low diagnostic accuracy (sensitivity 75–80 % and specificity 85–90 %). Recent reports show that other methods, such as simple ultrasound-based rules, subjective assessment and (Diffusion Weighted) Magnetic Resonance Imaging might be superior to the RMI in the pre-operative differentiation of adnexal masses.

**Methods/Design:**

A prospective multicenter cohort study will be performed in the south of The Netherlands. A total of 270 women diagnosed with at least one pelvic mass that is suspected to be of ovarian origin who will undergo surgery, will be enrolled. We will apply the Risk of Malignancy Index with a cut-off value of 200 and a two-step triage test consisting of simple ultrasound-based rules supplemented -if necessary- with either subjective assessment by an expert sonographer or Magnetic Resonance Imaging with diffusion weighted sequences, to characterize the adnexal masses. The histological diagnosis will be the reference standard. Diagnostic performances will be expressed as sensitivity, specificity, positive and negative predictive values and likelihood ratios.

**Discussion:**

We hypothesize that this two-step triage test, including the simple ultrasound-based rules, will have better diagnostic accuracy than the Risk of Malignancy Index and therefore will improve the management of women with adnexal masses. Furthermore, we expect this two-step test to be more cost-effective. If the hypothesis is confirmed, the results of this study could have major effects on current guidelines and implementation of the triage test in daily clinical practice could be a possibility.

**Trial registration:**

ClinicalTrials.gov: registration number NCT02218502

## Background

Ovarian cancer is the second most common gynecologic malignancy [1]. In 2008 it was the seventh leading cause of cancer deaths in women worldwide [1, 2]. Estimating the risk of malignancy is essential in the management of adnexal masses. Patients with a malignancy should undergo an appropriate staging procedure or debulking surgery carried out in specialized surgical centers. This is associated with a better median survival [3]. Vice versa, patients with a benign lesion may be managed conservatively or with minimal invasive surgery in non-specialized hospitals. This will limit morbidity and avoid unnecessary costs: laparoscopic surgery is associated with less blood loss, shorter hospital stay, and fewer postoperative complications with an improved quality of life and faster return to preoperative functioning [4].

There are several methods to distinguish benign from malignant adnexal masses. The commonly most used method in clinical practice is the Risk of Malignancy Index (RMI) [5–7]. The RMI is an easy to use scoring system that is recommended by many national guidelines in the differential diagnosis of ovarian masses. The RMI combines ultrasound variables, menopausal status and serum CA125 into a score used to predict the risk of ovarian cancer before surgery (Fig. 1). The reported sensitivity and specificity of RMI at a cut-off value of 200 are 75–80 % and 85–90 %, respectively [8]. This results in an incorrect diagnosis (false positive or false negative) in one out of five women with an adnexal mass. These patients therefore receive inappropriate treatment, potentially leading to increased morbidity and/or mortality.

**Fig. 1 Fig1:**
[figure not shown]
Schematic presentation of three different RMI score algorithms. This figure illustrates 3 different versions of the RMI score system: RMI-I [5], RMI-II [6] and RMI-III [7]. These versions differ from each other in the score attributed to the ultrasound features and menopausal status of the patient

The ‘simple ultrasound-based rules’ (simple rules) is another method to differentiate between benignity and malignancy. This method uses different morphological ultrasound features of adnexal masses (without including menopausal status or serum CA125 measurement). It includes 10 rules (Table 1); five rules to predict malignancy (M-rules) and five rules to predict a benign tumor (B-rules). If both or none of the M- and B-rules are met the test is inconclusive [9,10]. Simple rules are applicable in approximately 80 % of patients with an ovarian mass and in these cases a sensitivity of 95 % and a specificity of 91 % is achieved in previous studies [11].

**Table 1 Tab1:** Benign and malignant ultrasonic features used in simple ultrasound-based rules as proposed by Timmerman et al. [9]

10 Simple ultrasound-based rules	
B-features (for predicting a benign tumor)	
B1	Unilocular
B2	Presence of solid components, of which largest solid component has largest diameter <7 mm
B3	Presence of acoustic shadows
B4	Smooth multilocular tumor with largest diameter <100 mm
B5	No blood flow (color score 1)
M-features (for predicting a malignant tumor)	
M1	Irregular solid tumor
M2	Presence of ascites
M3	At least four papillary structures
M4	Irregular multilocular solid tumor with largest diameter ≥100 mm
M5	Very strong blood flow (color score 4)

*Rule 1*: If ≥ 1 M-features are present in absence of B-feature(s), the mass is classified as malignant

*Rule 2*: If ≥ 1 B-features are present in absence of M-feature(s), the mass is classified as benign

*Rule 3*: If both M-features and B-features are present, or if no B- or M-features are present, the result is inconclusive and a second stage test is recommended

In adnexal masses for which the simple rules yield an inconclusive result (unclassifiable masses), subjective assessment by Gray-scale and color Doppler ultrasound imaging by an experienced ultrasound examiner can be used as a second stage test to achieve an optimal diagnostic performance. This subjective assessment is also called ‘pattern recognition’ [12]. The downside of subjective assessment is that it is experience dependent. Nevertheless, subjective assessment by an expert sonographer seems to be superior to any scoring system or mathematical model when classifying adnexal masses [10, 13, 14]. However, it is neither feasible nor efficient that every patient would have to undergo an expert ultrasonography. Therefore, this method is very well suited as a second stage test. In cases where the simple rules were inconclusive (i.e., masses that are difficult to diagnose) subjective assessment was used successfully with a sensitivity of 91 % and a specificity of 93 % [10]. Several individual reports have confirmed that this two-step triage test is superior to the RMI, especially in terms of sensitivity [15–17].

Magnetic Resonance Imaging (MRI) with diffusion weighted sequences is another option for second stage testing of unclassifiable masses. The use of MRI – when interpret by specialized radiologists - also seems to be superior to RMI in the preoperative identification of adnexal masses. A meta-analysis performed by Dodge et al. resulted in an overall sensitivity of 92 % and a specificity of 88 % [18]. The test holds as an advantage that an MRI can not only distinguish a benign from a malignant mass, but can also detect possible metastases in case of a malignancy. Furthermore, MRI can help to select patients who might be more appropriately managed by neoadjuvant chemotherapy [19].

### Objectives

The primary objective of the SUBSONiC-study (Simple Ultrasound Based ruleS to differentiate OvariaN Cysts) is to test the hypothesis that the simple rules, supplemented -in case of an inconclusive result- with either subjective assessment by an expert sonographer or MRI, will give better diagnostic accuracy than the RMI and therefore will improve the management of women with adnexal masses. Since the RMI is now widely used, any result in favor of the triage test has the potential to alter future clinical practice and reduce costs. Based on the results a cost-effectiveness analysis will be performed.

Secondary objectives are to perform subgroup-analyses for premenopausal and postmenopausal women and to compare the diagnostic accuracy of subjective assessment by an experienced ultrasound examiner with MRI for those cases where the simple ultrasound-based rules were inconclusive. Furthermore, the study aims to assess various forms of interobserver-agreement: in the interpretation of MRI images between radiologists; in the interpretation of simple ultrasound-based rules between the primary ultrasound and the expert ultrasound; and in the subjective assessment between the primary ultrasound and the expert ultrasound. Last objective is to perform translational research and validate new biomarkers in the diagnosis of ovarian cancer.

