### Study procedures

Both RMI and simple rules will be performed in the regional hospitals and center hospital by general gynecologists during the same ultrasound scan. For collection of these variables a routine transvaginal ultrasound is sufficient. Transabdominal ultrasonography will be added if the mass is too large to be seen entirely by using only transvaginal ultrasonography. Gray scale and color Doppler ultrasound live images will be used to obtain all morphologic and blood flow variables to characterize each mass by RMI and by simple rules. The ultrasound will be performed by a general gynecologist or a trainee supervised by a general gynecologist. The sonographer will not be blinded for the serum CA125 level since this is needed to calculate the RMI.

Only when the simple rules are inconclusive the patient will be referred to the center hospital for the second stage tests; i.e., subjective assessment and MRI. From previous publications it can be deducted that this will be in approximately 20 % of patients.

Subjective assessment will be performed by an expert ultrasound examiner. The ultrasound examiner will be a level III sonographer according to the guidelines of the European Federation of Societies for Ultrasound in Medicine and Biology (EFSUMB-criteria), based on -among others- the years of experience, the hours of training and the total number of ultrasound scans performed by the operator [20].

The MRI will be performed at 1.5 Tesla (Intera; Philips Medical Systems, Best, The Netherlands). Conventional 2D T2-weighted sequences in three planes (sagittal, coronal, axial) and 3D T1-weighted sequences in the axial plane will be supplemented with diffusion weighted sequences. The MRI scans will be examined by 2 independent radiologists with experience in MRI, and who are blinded to the outcome of the subjective assessment. Furthermore, a blood sample will be taken for translational research purposes from patients with a mass that cannot be classified by simple rules. These serum samples will be stored for future biomarker studies.

A secured online Case Report Form (CRF) and database (‘MACRO’) are created in which the demographic data, ultrasound data and MRI data will be stored.

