### Analysis

#### Sample size calculation

The RMI has a relatively low sensitivity (75–80 %). By reducing the amount of false negative test results the patient will benefit most in terms of prognosis and survival. For the calculation of the sample size we therefore focused on sensitivity as the most important primary objective.

This study is designed to have an 80 % power to detect an increase of sensitivity from 79 % for the RMI to 91 % for the two-step triage test with a two-sided α value of 0.05. Using a matched pair design, it can be estimated that the total discordance between the preoperative diagnosis and the final diagnosis based on histology, obtained by surgery, is 20 % (16 % and 4 % respectively). Based on McNemar’s test a minimum sample size of 97 women with a malignancy is required [23]. Taking a prevalence of malignancy of 40 % into account, the study will need 243 patients in total. To allow for loss of power of 10 % a total of 270 women will be enrolled in the study.

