#### Statistical analysis

We will use McNemar’s test to determine the statistical significance of differences in sensitivity and specificity between the RMI and the two-step test. For statistical purposes borderline tumors will be classified as malignant tumors. The 95 % confidence intervals for sensitivity and specificity will be obtained using Wilson’s interval method [24].

Receiver operating characteristic (ROC) curves will be generated using Medcalc software version 12.7.7.0 (MedCalc Software bvba, Ostend, Belgium) to illustrate the predictive value of the chance of malignancy when using the RMI, simple rules, subjective assessment and MRI. The method described by DeLong et al. will be used for the calculation of the difference between two AUCs [25].

For the subgroup analysis of pre- and postmenopausal women stratification will be applied.

The interobserver-agreement will be evaluated with Cohen’s kappa (kappa values of 0.81–1.0 indicate very good agreement, kappa values of 0.61–0.80 good agreement, kappa values of 0.41–0.60 moderate agreement, kappa values of 0.00-0.40 poor agreement) [26].

Two-tailed *P*-values of ≤ 0.05 will be considered statistically significant for all statistical comparisons.

The economic evaluation will explore the potential cost-effectiveness of the triage test compared to RMI. Incremental cost-effectiveness is expressed as difference in the number of correct diagnosis (i.e., either true positive or true negative for malignancy based on histology) between both methods. With the usual care (RMI) 83 % of all adnexal masses are diagnosed correctly, versus 96 % with simple rules. The consequences of the difference in correct diagnosed patients between the various test are recharged in the treatment (costs of surgical management and hospital stay following surgery) and will therefore lead to a difference in cost-effectiveness.

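### The plan does not fix which triage strategy is compared with the RMI: the hypothesis says either second-stage test, inconclusive women get both, and one unnamed two-step test is sized and tested

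*Protocol article*

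**What the plan says.** - **Hypothesis (Objectives).** The simple rules, supplemented when inconclusive "with either subjective assessment by an expert sonographer or MRI, will give better diagnostic accuracy than the RMI".
- **Procedure (Study procedures).** When the simple rules are inconclusive, "the patient will be referred to the center hospital for the second stage tests; i.e., subjective assessment and MRI". Each such woman therefore has both results. A secondary objective confirms this, since it is to "compare the diagnostic accuracy of subjective assessment by an experienced ultrasound examiner with MRI for those cases where the simple ultrasound-based rules were inconclusive".
- **Sample size (Sample size calculation).** One comparison: "80 % power to detect an increase of sensitivity from 79 % for the RMI to 91 % for the two-step triage test".
- **Test (Statistical analysis).** McNemar's test is applied to "differences in sensitivity and specificity between the RMI and the two-step test", again in the singular. Two-tailed P-values of 0.05 or less "will be considered statistically significant for all statistical comparisons". No order of testing or adjustment is stated.
- **Intended use (Discussion).** Hospitals may adopt the simple rules with subjective assessment or the simple rules with MRI, according to local expertise and resources.
- **Conflicting results (Management of the mass).** Only conflict between the RMI and the triage result is covered, and only for patient care. Nothing is said about how a mass is classified for analysis when subjective assessment and MRI disagree.

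**The concern.** An either/or hypothesis, a procedure that yields both results and a test of one two-step test do not fit together. Two readings are possible, and each leaves a different gap.

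1. **Two strategies**, simple rules + subjective assessment and simple rules + MRI. Each can be tested against the RMI at 0.05 and either can be reported as the triage test. The primary error rate is then above 5%, and the choice can be made after the results are known.
2. **One composite test** that uses both second-stage results. There is then one comparison, but the index test result is undefined wherever subjective assessment and MRI disagree.

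The abstract, the Background (which presents MRI as another option for the second stage) and the Discussion favour the first reading, but no sentence settles it. The Objectives state that any result in favour of the triage test could change practice, so it matters which strategy that result belongs to.

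**Working it through.** **1. Reproduce the stated sample size.** Inputs from Sample size calculation: discordance 0.20 (0.16 and 0.04), two-sided α 0.05, power 80%, prevalence 40%, allowance 10%. The share of discordant pairs in favour of triage is 0.16/0.20 = 0.8.

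- Discordant pairs = (1.960 × 0.5 + 0.842 × √(0.8 × 0.2))² / (0.8 − 0.5)² = 19.26
- Malignancies = 19.26 / 0.20 = 96.3, rounded up to 97
- Total = 97 / 0.40 = 242.5, rounded up to 243
- Enrolled = 243 / 0.90 = 270

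The plan's figures reproduce exactly, for one comparison at 0.05.

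**2. Error rate if either strategy may carry the claim.** If the two tests were independent, the chance of at least one false positive would be 1 − 0.95² = 9.75%. They are not independent: when the simple rules are conclusive, both strategies give the same result.

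Assumptions: neither strategy differs from the RMI in sensitivity; discordance with the RMI is 20%, split 10%/10%; RMI sensitivity is 79%; 20% of malignancies are inconclusive.

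- If, in an inconclusive malignancy, subjective assessment and MRI are independent given the RMI result, both are discordant with probability 0.10²/0.79 + 0.10²/0.21 = 0.0603.
- Correlation of the two McNemar statistics = (0.8 × 0.20 + 0.2 × 0.0603) / 0.20 = 0.86.
- If the two tests coincide half the way from independence to full agreement, 0.0603 becomes (0.20 + 0.0603)/2 = 0.130 and the correlation is 0.93.

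From the bivariate normal distribution:

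| Correlation | At least one significant difference, two-sided (nominal 5%) | At least one false claim for triage (nominal 2.5%) |
|---|---|---|
| 0.86 | 7.4% | 3.7% |
| 0.93 | 6.7% | 3.4% |

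For inconclusive shares from 10% to 40% the two-sided figure runs from about 6.2% to 8.3%.

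**3. What each remedy does to the sample size.**

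- *One named primary strategy at 0.05, the other tested second in a fixed sequence:* 97/243/270 is unchanged and the error over both claims stays at 5%.
- *Either may succeed, 0.025 each:* (2.241 × 0.5 + 0.842 × 0.4)² / 0.09 / 0.20 = 118.0, so 118 malignancies, 118/0.40 = 295 women and 295/0.90 = 328 enrolled. With 97 malignancies, power per test falls from 80.3% to 69.2%.

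**The case against.** **The article is a condensed account, and multiplicity rules are usual SAP content.** This is right for part of the matter. The protocol states that "The MRI scans will be examined by 2 independent radiologists with experience in MRI"; which reading counts can be left to the SAP, and two readers are needed anyway for the agreement objective. It is not right for the main point. The article states a hypothesis, a procedure and a test that do not match, and it sets 0.05 for every comparison.

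**The effect is small.** It is. A triage strategy significantly worse than the RMI cannot support a claim that it is better, so the relevant rise is from 2.5% to 3.4–3.7%. On the Background's figures, assuming that the overall MRI accuracy holds in inconclusive masses, the two strategies are also nearly equal: sensitivity is 0.8 × 95 + 0.2 × 91 = 94.2% with subjective assessment and 0.8 × 95 + 0.2 × 92 = 94.4% with MRI. Similar expected values do not settle which strategy crosses 0.05 in one sample, so the freedom to choose remains.

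**Strategies that can be adopted separately may not need adjustment.** This is arguable, and putting one strategy behind the other sits uneasily with the Discussion. It would still have to be stated that there are two comparisons and which one the sample size serves.

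**Stronger readings that the documents do not support:**

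- *That both harms apply together.* They belong to alternative readings. With two strategies, disagreement between subjective assessment and MRI needs no joint class. No section proposes an either-positive or both-positive rule, so accuracy figures built on such rules do not describe this plan.
- *That the primary error is far higher because specificity is tested too.* One strategy tested on both measures would already give 1 − 0.95² = 9.75% if the tests are independent, so most of that excess has nothing to do with the unnamed index test. Sample size calculation also gives sensitivity priority.
- *That the design value of 91% shows subjective assessment was meant.* The Background's 91% is its sensitivity within inconclusive masses; the design's 91% is for the whole two-step test, for which the Background's figures give 94.2%.

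**Conclusion.** The point holds. The primary index test is not identified, and the sample size covers one comparison where the procedures generate two. On the two-strategy reading, the chance of at least one false significant sensitivity difference is about 6.7–7.4% instead of 5%, and of a false claim for triage about 3.4–3.7% instead of 2.5%. These figures rest on no true difference for either strategy, 20% discordance split equally, a 20% inconclusive share among malignancies, and the normal approximation. On the composite reading the error rate is not inflated, but the test result is undefined where the second-stage tests disagree.

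The inflation is modest. The larger weakness is that the strategy presented as the triage test could be chosen after the results are seen. A reader might infer that the sample size is wrong; it is not, for one named comparison.

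**What to change.** Reconcile Objectives, Study procedures, Sample size calculation and Statistical analysis as follows:

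1. Name one primary comparison, on sensitivity, by McNemar's test at two-sided 0.05. One option is simple rules + subjective assessment versus the RMI at 200, because the Background uses the term two-step triage test for that combination.
2. Test the other strategy against the RMI on sensitivity second, at 0.05, only if the first comparison is significant.
3. Treat specificity and all other comparisons as secondary, and limit the blanket 0.05 statement accordingly.
4. If a single composite was intended instead, say so and define, for analysis only, the class of a mass on which subjective assessment and MRI disagree.

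The MRI reading that counts can be specified in the SAP.

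**Cost.** Under steps 1 to 3 only analysis wording changes; 97/243/270 stands and patient care is untouched. The second strategy can be claimed only if the first succeeds. If both have the planned effect and the correlation is 0.86 to 0.93, the chance of claiming the second with 97 malignancies is about 74 to 76%, against 80.3% if it were tested alone. Letting either strategy succeed at 0.025 would avoid the ordering but need 328 women.

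### Primary-versus-expert agreement on the simple rules can be estimated only in primary-inconclusive masses, where a kappa on the overall classification carries no information

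*Protocol article*

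**What the plan says.** All references are to the protocol article.

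- **Objectives.** One of several agreement aims is agreement "in the interpretation of simple ultrasound-based rules between the primary ultrasound and the expert ultrasound". It is not restricted to any subset of masses, and it does not say whether the rating is the overall classification or the single features.
- **Statistical analysis.** One statistic covers all the agreement aims: "The interobserver-agreement will be evaluated with" Cohen's kappa, with values from 0.00 to 0.40 labelled poor.
- **Study procedures.** "Only when the simple rules are inconclusive the patient will be referred to the center hospital for the second stage tests". The expected share is given: "From previous publications it can be deducted that this will be in approximately 20 % of patients".
- **Study procedures, first scan.** "Both RMI and simple rules will be performed in the regional hospitals and center hospital by general gynecologists during the same ultrasound scan". Women seen at the center hospital therefore start with a general gynecologist too.
- **Background.** The article rejects a universal expert scan: "it is neither feasible nor efficient that every patient would have to undergo an expert ultrasonography".
- **Table 1, Rule 3.** The rules have a third outcome besides benign and malignant: "If both M-features and B-features are present, or if no B- or M-features are present, the result is inconclusive".

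**The concern.** The agreement aim needs two simple-rules ratings of the same mass, one from the primary examiner and one from the expert. The referral rule produces that pair only when the primary rating has already come out as inconclusive. Selecting women on one rater's result removes that rater's variation, and kappa cannot work without it.

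What is at stake is a secondary result that is either fixed in advance or wider in scope than its data. A zero labelled poor could be read as evidence that general gynecologists apply the rules unreliably, and the two-step strategy relies on them for its first step. A feature-level kappa reported without its restriction could be read as describing the rules across all adnexal masses, although it would come only from those the primary examiner could not classify.

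**Working it through.** The plan states no expected kappa, so the only figures of its own to reproduce are the ones that fix the number of women involved.

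**Step 1. Number of women with both ratings.**
- Women with a malignancy, by the conditional McNemar formula with discordance 0.16 and 0.04: ψ = 0.16/0.20 = 0.80. Discordant pairs m = [1.96 × 0.5 + 0.8416 × √(0.80 × 0.20)]² / (0.80 − 0.50)² = 19.26. Then n = 19.26/0.20 = 96.3, rounded up to 97, as stated.
- Total: 97/0.40 = 242.5, so 243; 243/0.90 = 270. Both match the plan.
- Women expected to have an expert scan: 0.20 × 270 = 54 (0.20 × 243 ≈ 49 without the allowance).

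**Step 2. Kappa on the three-way classification.** Kappa = (po − pe)/(1 − pe), where po is observed and pe is chance agreement. Among referred women the primary rating is always inconclusive. Let q be the share that the expert also calls inconclusive.
- po = q, because the raters agree only when the expert says inconclusive too.
- pe = 0 × P(expert benign) + 0 × P(expert malignant) + 1 × q = q.
- Kappa = (q − q)/(1 − q) = 0 for every q below 1. At q = 1 it is 0/0, which is undefined.

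Numerically, with n = 54:

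| q | po | pe | kappa |
|---|---|---|---|
| 0 | 0 | 0 | 0 |
| 0.20 | 0.20 | 0.20 | 0 |
| 0.50 | 0.50 | 0.50 | 0 |
| 0.80 | 0.80 | 0.80 | 0 |
| 0.95 | 0.95 | 0.95 | 0 |
| 1 | 1 | 1 | undefined |

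Even 95 % raw agreement gives zero. Sample size does not enter, so more data would not help.

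**Step 3. What the selection hides.** Assume, for illustration only, that all 270 women were rated twice (rows primary, columns expert; order benign, malignant, inconclusive): 119, 4, 7 / 5, 71, 10 / 14, 10, 30.
- po = (119 + 71 + 30)/270 = 0.815.
- pe = (130 × 138 + 86 × 85 + 54 × 47)/270² = 0.381.
- Kappa = (0.815 − 0.381)/(1 − 0.381) = 0.70, which falls in the plan's good band.

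Keep only the third row, the 54 women who would be referred: po = 30/54 = 0.556, pe = 0.556, kappa = 0. The raters and masses are the same, and only the referral filter has changed. The 0.70 depends on the assumed table; the zero does not.

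**Step 4. Kappa on a single feature.** By Rule 3 an inconclusive mass shows both kinds of feature or none, so the primary rating of any one feature can still vary. With an assumed 2 × 2 table for 54 women (20 both present, 24 both absent, 4 and 6 discordant):
- po = 44/54 = 0.815.
- pe = (24 × 26 + 30 × 28)/54² = 0.502.
- Kappa = (0.815 − 0.502)/(1 − 0.502) = 0.63.

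A feature-level kappa can therefore be estimated, but only within masses selected on the primary examiner's own feature ratings.

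**The case against.** The strongest reply is that the article never plans a kappa on the three-way classification. It speaks of interpreting the rules, it describes the method as ten rules, and interpreting them may well mean judging each feature. Step 4 shows that kappa is then not degenerate. The choice of unit is also the kind of detail that a full protocol or analysis plan settles. This stands in part: a reader might infer that the plan is bound to report a kappa of zero, and the wording does not support that. It does not remove the point. The aim, the statistic and the referral rule are all stated, and under either reading agreement is estimable only in primary-inconclusive masses, a limit that the objective does not mention. Nothing in the article provides an expert scan or a re-read for conclusive cases, and Study procedures says that live images are used.

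A second reply is that a table with a single occupied row would be noticed before publication. It probably would, and the aim is secondary, with no role in the McNemar comparison or the sample size. That limits the severity but is no reason to keep the ambiguity.

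A reader might also infer that the companion aim, agreement on subjective assessment, is impossible because the primary examiner records no such judgement. The article does not support this. Study procedures does not list every recorded item, the case report form is not shown, and the aim itself presupposes a primary subjective call.

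**Conclusion.** The point holds in a limited form. As described, primary-versus-expert agreement on the simple rules can be estimated in about 54 of 270 women, all inconclusive on the primary scan. On the overall classification, kappa is 0 whatever mix the expert records, or undefined if the expert calls every mass inconclusive, and it says nothing about the observers. On the single features, kappa can be estimated but describes only the selected masses.

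The zero is algebra and needs no assumption beyond the stated referral rule. The count of 54 rests on the plan's own 20 %. The kappas of 0.70 and 0.63 come from assumed tables and only illustrate. The primary comparison of RMI with the two-step test is unaffected. This should be corrected, but it does not threaten the main result.

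**What to change.** In Objectives and Statistical analysis:

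1. State that no kappa will be computed between primary and expert ultrasound on the overall simple-rules classification, because the primary result is constant in the women who have both scans.
2. Define the agreement analysis at feature level (B1 to B5, M1 to M5): percent agreement with a 95 % confidence interval, and kappa, labelled in text and tables as applying to primary-inconclusive masses only.
3. Report the proportion of these masses that the expert can classify as benign or malignant with the same rules, and the accuracy of those classifications against histology. This is the informative form of the classification question that the design allows.

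The cost is a few sentences of wording and no extra scans. The downside is that the study will make no agreement statement for masses that the primary examiner could classify. If that statement is wanted, expert ratings would be needed in at least a sample of women with a conclusive primary result, which the present design does not provide.
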